## Abstract

**Background:**

Faced with the increase in the number of chronic diseases with the aging of the population, and with the observation of the insufficiency of therapeutic control, a new need has emerged, that of having a patient as a partner in care.

**Methods:**

This study is a randomized controlled trial. Patients with coronary heart disease will be recruited from one clinical site and randomly assigned into two groups: the intervention group and the control group. All participants will be followed up for a total of one year (with three-time points for data collection). Patients who are assigned to the intervention group will receive therapeutic education at first. The digital platform will then allow healthcare providers to accompany them outside the hospital walls. The primary outcome is the incidence of major cardiovascular events within one year of discharge. Main secondary outcomes include changes in health behaviors, medication adherence, and quality of life score. The digital platform is a multi-professional telemonitoring platform that allows care teams to accompany the patient outside the hospital walls. It allows the collection and transmits information from the patient’s home to the therapeutic education team. All data will be secured at a certified host. The patient application provides data on compliance, adherence to physical activity (number of steps taken per day), adequate diet (weight gain, food consumed during the meal, compliance with low-salt or salt-free diet, diabetic diet), smoking cessation, as well as medication adherence. Access to educational tools (digital media) is provided to all initial program participants. These tools will be updated annually by the rehabilitation team on the recommendations. The platform also offers the possibility of organizing an individual or group remote educational session (videoconference modules allowing group and individual sessions), a secure integrated caregiver-patient messaging system. The control group will receive the usual controls at the hospital.

**Discussion:**

To offer a complete solution of care to our patients, we have thought of setting up a digital platform that aims to monitor the patient and strengthen their abilities to manage their condition daily. This pilot experience could be generalized to several services and disciplines. It could be used in several research works.

**Trial registration:**

Trial registered with the Pan African Clinical Trial Registry (PACTR202307694422939). URL: https://pactr.samrc.ac.za/TrialDisplay.aspx?TrialID=24247.

## Introduction

Cardiovascular disease remains a leading cause of death worldwide including in Tunisia, with about 49% of the deaths from coronary heart disease (CHD) [1, 2].

Faced with the increase in the number of chronic diseases with the aging of the population, and with the observation of the insufficiency of therapeutic control, a new need has emerged, that of having a patient as a partner in care.

Participatory medicine involves a collaborative approach between patients and healthcare professionals, where patients are actively engaged in making decisions about their own treatment. This fosters better mutual understanding and enables more precise customization of medical care.

Therapeutic patient education (TPE) is a humanistic approach centered on the patient, his needs, and resources. It is proposed not only to help the patient understand the disease and treatment but also to help them become autonomous.

In fact, TPE is an approach to facilitate patient and family learning about the treatment of disease and the adoption of self-management behaviors and lifestyles to improve physical and psychosocial health outcomes (eg, biomarkers, quality of life) [3]. The goal of TPE is to improve health outcomes, including by preventing avoidable complications [4]. In prior studies, investigators have reported the positive impact of TPE on knowledge, behavioral, psychosocial, and health outcomes [5].

The appropriate application of the TPE program should result in a better quality of life for people with coronary heart disease. However, the success of these measures depends largely on the skills of patients in the daily management of their condition. Patients with coronary heart disease are often not adequately supported to develop skills in the day-to-day management of their health condition [6].

However, in most TPE programs, patient follow-up stops after the end of the education program. It is essential to assist patients with coronary heart disease in the third phase of their management.

In fact, addressing cardiovascular health in disease management was associated with a 68% and 45% reduction of incident major cardiovascular events and coronary heart disease mortality, respectively [7–9]. However, a low prevalence of ideal cardiovascular health was identified among patients with coronary heart disease, despite interventions in facilitating cardiovascular health have been developed and implemented [10–13].

Thus, our study aims to create a digital platform allowing the follow-up of patients after having benefited from a therapeutic patient education program.

This is an innovative project in our Tunisian context that offers new modes of monitoring and therapeutic support to patients suffering from cardiovascular pathology. Indeed, it is the 1st digital platform for monitoring patients with coronary heart disease in Tunisia.

This digital tool represents an innovation both for patients, who are offered a personalized monitoring and learning program tailored to their profile and wishes; and for healthcare professionals, who now have at their disposal a tool for monitoring patient objectives and modules for learning new skills.

This pilot experiment could be extended to several departments and disciplines.

This study protocol is aimed to describe the implementational plan for a controlled clinical trial in which the effect of the digital platform on major cardiovascular events reduction for patients with coronary heart disease will be evaluated. Meanwhile, the study plan for testing the effects of the TPE on facilitating adherence to recommended health behaviors (including healthy diet, regular physical activity, and smoking cessation) and medications will also be described.

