**Fig 1 pone.0300250.g001:**
[figure not shown]
The schedule of enrolment, interventions, and assessments *. *Recommended content can be displayed using various schematic formats. See SPIRIT 2013 Explanation and Elaboration for examples from protocols. **List specific timepoints in this row.

Patients will be included in the study if they: (a) are 18 years or older; (b) have a documented diagnosis of coronary heart disease including acute myocardial infarction (AMI) (Non ST and ST elevation MI), patients with unstable angina, and patients with stable angina; (c) have access to a computer, and (d) agree to participate.

The exclusion criteria include: patients who are (1) with a history of psychiatric and neurological disorders; (2) unable to speak or understand Arabic; (3) with impaired bilateral hearing, or visual impairment which limits the use of computers; (4) with contraindications or severe physical disabilities that limit patients from participation; Additional exclusion criteria will be applied if patients are not able to understand the procedure and the aims of the study after full explanation.

By using the results of a meta-analysis published in 2017 [5] for an incidence of a major cardiovascular event of 13.8% in the intervention group and 38.6% in the control group, with a power of 80% and a first-species risk α of 0.05, we found a size of 56 patients in each group.

All investigators in this study will attend rigorous training on data collection and research protocol.

Training sessions will be thorough, and detailed. The purpose of this rigorous training is to ensure that all investigators have a comprehensive understanding of the data collection methods and research protocols relevant to the study.

The research protocol encompasses the set of guidelines, procedures, and ethical standards that govern how the research study will be conducted. It includes considerations such as participant recruitment, informed consent, data handling, confidentiality, and data analysis methods.

These sessions will be held before the start of the survey to prevent measurement bias. In addition, all investigators are trained in the principles of therapeutic education.

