### Intervention

To identify eligible patients, a targeted review of patients’ medical record based on the inclusion and exclusive criteria will be carried out, with referrals from nurses or clinicians within the study site. During the formal screening session, we will ask patients to complete an initial screening assessment which includes age, educational background, diagnosis, heart function grade, etc. Patients who meet the study criteria will be asked to sign a written informed consent before attending the baseline visit. Participants’ baseline data includes patients’ general characteristics, health behaviors (daily diet, physical activities, smoking status) and medication adherence, as well as their blood pressure, blood glucose, blood lipid levels during hospitalization.

A total of 112 patients with coronary heart disease will be recruited at a clinical site and divided equally into an intervention group and a control group. All participants will be followed up for a total of one year (with three time-points for data collection).

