### Intervention group

Patients assigned to the intervention group will first receive therapeutic education. The digital platform will then enable care providers to support them remotely.

A questionnaire will be distributed to patients before they begin the TPE program, in order to assess their knowledge of the disease, their eating habits, their physical activity, etc.

The same questionnaire will be distributed again at the end of the intervention, to study the impact of the TPE program in terms of knowledge retention.

Participants assigned to the intervention group will be divided into sub-groups. Each group will receive three TPE sessions. Educational sessions will be held once every week.

TPE sessions will include theoretical presentations on the pathophysiology of coronary artery disease, its risk factors, therapeutic objectives and therapeutic management.

These sessions will also include practical workshops using video sequences, role-playing and card games, covering heart attack alert, biological and blood pressure therapeutic objectives, the Mediterranean diet, the different commercial presentations of drugs, and types of social coverage.

At the end of each session, a round-table discussion will be held on the daily life of a coronary sufferer: physical activity/stress management/smoking/returning to work.

During the last session, each patient will benefit from an individual interview during which a lipid and glycemic assessment will be requested to evaluate the impact of the TPE in the medium term.

In addition, each patient will receive leaflets in Arabic, summarizing what will be presented during the TPE sessions.

At 3 months after completion of the TPE program, the same questionnaire will be redistributed, a biological check-up will be requested, and a quality-of-life assessment will be carried out.

In a second phase, the intervention group will be monitored via a digital platform.

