### Control group

The control group will receive the usual controls at the hospital. Patients of the control group will not receive the TPE program neither a digital monitoring.

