### Outcomes

#### Primary outcome

The primary outcome of this study is the occurrence of major cardiovascular events in the year following hospital discharge for the control group, and in the year following completion of the TPE program with digital follow-up for the intervention group.

The primary outcome is based on the occurrence of acute myocardial infarction, stable angina, coronary revascularization, stroke, hospitalized heart failure, or death attributable to any cardiovascular disease [15]. Information on the primary outcome will be systematically obtained through follow-up interview at 12 months and confirmed by reviewing patients’ medical records. If a patient dies during follow-up, this information will be obtained directly from patient’s family or confirmed by physician.

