## Discussion

Many studies have highlighted the impact of therapeutic education on better compliance by coronary patients, and on reducing the incidence of major cardiac events [3–5, 18–23].

However, the impact of digital patient monitoring is still poorly elucidated, especially in developing countries such as Tunisia.

In fact, a few studies carried out in developed countries have reported the benefits of using telephone applications to monitor coronary patients [24–26]. Besides, although numerous studies have been implemented with individualized mHealth-based interventions, the long-term effects of such interventions on the reductions of major cardiovascular events have not been well established. The influence of individualized mHealth based interventions on major cardiovascular events was also not determined due to small sample sizes in previous studies [25, 26].

Our work will focus on the impact of third-phase computerized follow-up of coronary patients on the incidence of major cardiac events.

In addition, the daily follow-up of these patients, together with a communication interface enabling them to report on their daily lives, will make it possible to monitor changes in their lifestyles and thus redress misbehavior prospectively.

This pilot experience could be generalized to several services and disciplines. It could be used in several research works.

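### The stated aim is the digital platform's effect on cardiovascular events, but the randomised comparison can only test education plus platform against usual care

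*Protocol article*

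**What the plan says.** The last paragraph of the Introduction gives the main purpose as a trial "in which the effect of the digital platform on major cardiovascular events reduction for patients with coronary heart disease will be evaluated". It then names a second, separate purpose: "the study plan for testing the effects of the TPE on facilitating adherence to recommended health behaviors", and on medication use. The Discussion restates the first: "Our work will focus on the impact of third-phase computerized follow-up of coronary patients on the incidence of major cardiac events".

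The arms are described elsewhere. Under Intervention, the 112 patients are "divided equally into an intervention group and a control group". Under Intervention group: "Patients assigned to the intervention group will first receive therapeutic education. The digital platform will then enable care providers to support them remotely". Under Control group: "Patients of the control group will not receive the TPE program neither a digital monitoring".

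Two places already describe the package. The Methods part of the Abstract puts education first and the platform after it. The Primary outcome section counts events "in the year following completion of the TPE program with digital follow-up for the intervention group", and in the year after discharge for controls.

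The Discussion opens by crediting therapeutic education with fewer major cardiac events. It then says that the impact of digital monitoring is still unclear.

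**The concern.** The aim attributes the primary result to one component, while the design varies two together. If the intervention arm has fewer events, education, the platform or both could be responsible, and the protocol itself regards education as effective. The question it calls unsettled, what digital monitoring contributes, is the one the comparison leaves open.

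This bears on use of the result. The Introduction and Discussion both raise extension to other departments or services and disciplines. A positive result read in the terms of the stated aim would be taken as evidence for the platform, which the data could not support.

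**Working it through.** **1. What differs between the arms** (Intervention group, The therapeutic digital platform, Control group)

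| Arm | TPE sessions | Digital platform |
|---|---|---|
| Intervention | three, weekly | yes, after TPE |
| Control | none | none |

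There is no TPE-only arm, no platform-only arm and no second randomisation after TPE. The two components are fully confounded with arm.

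**2. What the comparison estimates.** Write the one-year event risks as C (usual care), T (TPE alone) and TP (TPE plus platform). Then

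C − TP = (C − T) + (T − TP).

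The trial observes C and TP. The platform's effect, given after TPE as here, is T − TP. T is never observed, so there is one equation with two unknowns. No analysis of the planned randomised comparison recovers T − TP.

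**3. The plan's own figure.** Inputs from Settings and participants: 13.8% and 38.6%, power 80%, α 0.05. Sidedness is not stated; two-sided is assumed. The difference is 0.386 − 0.138 = 0.248 and the mean rate is 0.262.

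- Uncorrected n = [1.960·√(2·0.262·0.738) + 0.842·√(0.138·0.862 + 0.386·0.614)]² / 0.248² = 48.15, rounded up to 49.
- With continuity correction, n′ = (48.15/4)·[1 + √(1 + 4/(48.15·0.248))]² = 55.9, rounded up to 56.

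The stated 56 per group reproduces. It is the size for C versus TP, the package contrast.

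**4. Does the later time origin isolate the platform?** The intervention arm's year starts after TPE (Primary outcome). That does not remove education from the comparison: any lasting effect of TPE runs through that year, and controls never had TPE. It also gives the arms different starting points.

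**5. The separate TPE aim.** Intervention group plans a questionnaire before TPE, again at its end, and again 3 months after completion, when laboratory tests and quality of life are added. It then describes platform monitoring as a following phase. The first step under The therapeutic digital platform instead checks eligibility and enrols patients when TPE ends. On the first account the 3-month assessment precedes the platform; on the second it may fall after exposure has begun. The end-of-TPE questionnaire could precede the platform on either account. These assessments are described only for the intervention arm. Whether controls have a matching one depends on the three data-collection time points in Fig 1, which is not shown.

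**6. Illustration only.** A platform contrast would be T versus TP. The documents give no T. Assume TP = 13.8% and that TPE accounts for 25%, 50% or 75% of the 24.8 points:

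- T = 38.6 − 0.25·24.8 = 32.4%, 38.6 − 0.50·24.8 = 26.2%, or 38.6 − 0.75·24.8 = 20.0%.
- By the method of step 3, about 90, 178 or 605 per arm would be needed.

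These shares are assumptions. They show only that 56 per group was not derived for a platform contrast.

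**The case against.** The strongest reply is that the package was always meant. The Abstract, the arm descriptions and the primary outcome all set it out, the control section is plain, and testing a complex intervention as a whole against usual care is a legitimate choice. That stands, and it is why the design need not change. It does not rescue the sentences on aim and focus, which name the platform alone and so contradict the operative text. Limitations does not repair this either: it notes that controls lack full platform access, but not that they also lack TPE or that the components cannot be separated.

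Four stronger readings are tempting, and the documents do not support them.

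- *No TPE effect can be examined at all.* A questionnaire at the end of TPE is planned and could precede the platform. It would be a before-and-after measure unless controls have a counterpart, but it is not ruled out.
- *The whole 24.8-point difference could be due to TPE.* That is a logical bound for any package containing TPE, not an estimate. The rates come from reference 5, which the Introduction cites for TPE. The reference is not at hand, so what its interventions contained cannot be checked.
- *The sample size is wrong.* It reproduces for the package contrast, and the source of its rates is stated. TPE evidence is a relevant basis for a package that includes TPE, so relabelling that assumption would be editorial.
- *The authors will publish the result as proof of the platform.* The documents contain no planned conclusion to that effect. What can be corrected is the stated aim.

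**Conclusion.** The point holds for the primary objective. As written, the Introduction and Discussion pose a question about the platform alone, which the two-arm comparison cannot answer. What it can answer is whether TPE followed by digital follow-up changes the incidence of major cardiovascular events relative to usual care. The mismatch affects the attribution of the primary result. It does not affect the package comparison as such or the sample-size arithmetic. The platform's share has no calculable size, because the documents supply no rate under TPE alone.

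For the TPE aim on behaviours and adherence the conclusion is weaker. Outcomes measured after the platform starts belong to the package. Earlier ones may speak to TPE, subject to the unresolved platform start and to whether controls are assessed at the same time.

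**What to change.** - In the Introduction and Discussion, restate the primary objective and the permitted conclusion as the effect of TPE followed by digital follow-up, as a package, versus usual care.
- In Limitations, add that the contributions of education and platform cannot be separated.
- Limit any TPE-specific claim on behaviours and adherence to measurements taken before platform exposure, and call it uncontrolled unless controls have a matching assessment. Attribute later outcomes to the package.
- Reconcile Intervention group with the first step under The therapeutic digital platform on when the platform starts relative to the 3-month assessment.

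The cost is a narrower claim: the platform question stays open. Arms, visits and sample size are unchanged.

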## Materials and methods

### Study design

This study is a controlled clinical trial. The trial has been registered at the Pan African Clinical Trial Registry (PACTR202307694422939) after enrolment of the first participant.

The results will be reported according to the CONSORT guidelines [14]. This study is approved by the Institutional Review Committee of Sahloul University Hospital (Approval No. HS12-2022). Written informed consent will be obtained from all patients who meet the inclusion criteria and are willing to participate before randomization.

### Settings and participants

Eligible patients will be recruited from the department of cardiology of Sahloul university hospital over one month. All participants will be followed up for a total of one year (with three time-points for data collection) (Fig 1).

**Fig 1 pone.0300250.g001:**
[figure not shown]
The schedule of enrolment, interventions, and assessments *. *Recommended content can be displayed using various schematic formats. See SPIRIT 2013 Explanation and Elaboration for examples from protocols. **List specific timepoints in this row.

Patients will be included in the study if they: (a) are 18 years or older; (b) have a documented diagnosis of coronary heart disease including acute myocardial infarction (AMI) (Non ST and ST elevation MI), patients with unstable angina, and patients with stable angina; (c) have access to a computer, and (d) agree to participate.

The exclusion criteria include: patients who are (1) with a history of psychiatric and neurological disorders; (2) unable to speak or understand Arabic; (3) with impaired bilateral hearing, or visual impairment which limits the use of computers; (4) with contraindications or severe physical disabilities that limit patients from participation; Additional exclusion criteria will be applied if patients are not able to understand the procedure and the aims of the study after full explanation.

By using the results of a meta-analysis published in 2017 [5] for an incidence of a major cardiovascular event of 13.8% in the intervention group and 38.6% in the control group, with a power of 80% and a first-species risk α of 0.05, we found a size of 56 patients in each group.

All investigators in this study will attend rigorous training on data collection and research protocol.

Training sessions will be thorough, and detailed. The purpose of this rigorous training is to ensure that all investigators have a comprehensive understanding of the data collection methods and research protocols relevant to the study.

The research protocol encompasses the set of guidelines, procedures, and ethical standards that govern how the research study will be conducted. It includes considerations such as participant recruitment, informed consent, data handling, confidentiality, and data analysis methods.

These sessions will be held before the start of the survey to prevent measurement bias. In addition, all investigators are trained in the principles of therapeutic education.

